#### Baseline laboratory assessments

Data will be used from the last routine assessment as indicated by the national guideline [47]: Hb, Ht, phosphate, calcium, parathyroid hormone (PTH); spKt/V urea (monthly). Residual kidney function will be expressed as the estimated GFR (eGFR), calculated by the mean of 24-h urinary creatinine and urea clearances and adjusted for body surface area (mL/min/1.73 m2). The plasma concentrations used for this calculation are the mean of the values before and after dialysis. eGFR is considered zero in patients with a urinary production < 100 mL/day.

#### Dialysis-related recordings

Before dialysis, the bodyweight and the interdialytic weight gain (IDWG) of the patients will be noted. During dialysis, hemodynamics will be recorded according to the protocol (see below) as well as all other treatment related variables, including UF volume, UF rate and online monitoring of estimated Kt/V from UV-absorbance measurements in spent dialysate via Adimea® [50]. Furthermore, data on the anticoagulation type and dose, vascular access (central venous catheter [CVC], graft or AV fistula, including documentation of distance between arterial needle and anastomosis in the 2 latter, vascular access flow (if fistula or graft), needle size and type, blood pump speed, dialysis machine and dialyzer. In case of HDF treatment, the achieved convection volume will be noted at the end of each procedure. Convection volumes will be calculated as the sum of the intradialytic weight loss and the substitution volume in L/session. Finally, at the end of each dialysis procedure the patients achieved dry weight will be recorded.

#### Patient tolerance

Since simple questions on intradialytic symptoms appear to predict patient outcomes better than complicated questionnaires [51–53], a modified version of the Dialysis Symptom Index (DSI) will be handed out after each treatment period (Table 3). Thermal perception will be assessed by the Visual Analogue Scale - Thermal Perception (VAS-TP) [54, 55], before HD(F) and after 1 and 3 h (Fig. 2). Upon a continuous line, patients can indicate their actual thermal perception.

**Table 3 Tab3:** Modified Dialysis Symptom Index (DSI)

During the past week: did you experience this symptom?	Not at all	A little bit	Some-what	Quite a bit	Very much
1. Dizziness or lightheadedness	0	1	2	3	4
2. Nausea	0	1	2	3	4
3. Vomiting	0	1	2	3	4
4. Headache	0	1	2	3	4
5. Muscle cramps	0	1	2	3	4
6. Swelling of the legs	0	1	2	3	4
7. Shortness of breath	0	1	2	3	4
8. Chest pain	0	1	2	3	4
9. Itching	0	1	2	3	4
10. Feeling cold	0	1	2	3	4
11. Shivering	0	1	2	3	4
12. Feeling tired or lack of energy	0	1	2	3	4
13. Recovery time after dialysis: 0 = none 1 = after 1 h 2 = after half a day 3 = the next day 4 = the day of the next dialysis	0	1	2	3	4
Are there any other symptoms not mentioned on this questionnaire that you have experienced during the past week?

**Fig. 2 Fig2:**

Visual Analogue Scale – Thermal Perception (VAS-TP). Thermal perception will be assessed by the Visual Analogue Scale - Thermal Perception (VAS-TP) before HD(F) and after 1 and 3 h. Upon the continuous line patients can indicate their actual thermal perception

#### Hemodynamic monitoring

Diastolic (DBP) and systolic (SBP) blood pressure, pulse pressure (SBP minus DBP), mean arterial pressure (MAP: [(SBP + 2*DBP)/3]), heart rate (HR) and intradialytic hypotensive episodes (IDH, see Primary endpoint) will be recorded before, after and during each dialysis treatment every 30 min (during the first week of every treatment modality) and every 15 min (during the second week). Measurements will be performed with a manometric cuff in different sizes, which is connected to the dialysis machine (automatic blood pressure measurement cuff, B. Braun Avitum AG, Melsungen, Germany).

#### Non-invasive advanced hemodynamic monitoring

During the first or second dialysis of the last week of every treatment modality, every 20 seconds MAP, stroke volume (SV), heart rate, total peripheral resistance and cardiac output (CO) will be obtained using the Clearsight monitor (BMEYE/Edwards Lifesciences, Amsterdam, The Netherlands), which is a non-invasive arterial pressure measuring device. This monitor turns finger arterial pressure with a fast-pneumatic system to account, as well as photoplethysmography to detect changes in finger arterial diameter during inflations [56]. A volume clamp method is used whereby rapid variations in the cuff pressure allow maintenance of a constant arterial diameter, with an automatic algorithm (Physiocal). The pressure within the cuff is therefore reflective of finger arterial pressure [56]. The Clearsight finger cuff will be attached to the mid-phalanx of the third digit of the hand at the contralateral side of the dialysis shunt. The heart reference system will be placed on the middle of the left side of the thorax. The measured hand and the manometric arm cuff are placed at the mid-thorax to account for hydrostatic pressure differences.

#### Body temperature

Body temperature will be assessed before and after each dialysis session by a tympanic thermometer (Genius 2 Tympanic Thermometer, Covidien, Mansfield, USA).

#### 2D speckle tracking echocardiography

Speckle Tracking Echocardiography (STE) will be performed before, after 1 and after 3 h of treatment during the last dialysis of each modality. Two-dimensional left ventricular (LV) measurements of wall thickness and cavity diameters, 2D biplane Simpson measurement of volumes and ejection fraction are measured using a commercial scanner (Affiniti 70C, Philips Healthcare, The Netherlands) with a fully sampled matrix array (S5–1) transducer. These measurements are indexed for body surface area (BSA). For the assessment of global longitudinal deformation (GLS) as well as distribution of regional longitudinal strain, 2DSTE is performed from an apical position. Diastolic LV function is measured by 2D LAVI (left atrial volume index), transmitral E/A ratio and deceleration time, e’ wave velocity, E/e’ ratio and SPAP (systolic pulmonary artery pressure). Estimated right ventricular function will be done by TAPSE (tricuspid annular plane systolic excursion), s’ wave velocity and RV (right ventricular) regional and global strain. The data will be recorded electronically and assessed off-line by a trained research physician in Xcelera Cardiology Information Management Version 4.1 (Philips Healthcare, The Netherlands).

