## Methods

### Study design

The HOLLANT study is an open, cross-over, multicenter, intervention RCT in chronic intermittent dialysis patients who will be exposed to four different dialysis modalities: 1) S-HD: HD with a dialysate temperature of 36.5 °C. 2) C-HD: HD with a dialysate temperature 35.5 °C. 3) LV-HDF: HDF with a convection volume of 15 L/1.73 m^2^/session and a dialysate temperature of 36.5 °C. 4) HV-HDF: HDF with a convection volume of ≥23 L/1.73 m^2^/session and a dialysate temperature of 36.5 °C.

After enrollment, participants will be randomized centrally to the four dialysis modalities by using computer randomization software [46]. Randomization occurs in blocks. Enrolled patients will be treated with their usual dialysis modality (either HD or HDF) during the first 2 weeks of the study. Patients who cannot achieve or tolerate a blood flow rate ≥ 350 mL/min during this run-in phase will be excluded before the actual start of the study. Treatment times will be fixed at 4 h per session during the entire conduct of the study. Thereafter, patients start the study-phase and will be treated with S-HD, C-HD, LV-HDF or HV-HDF in a random order. Each dialysis modality will last 2 weeks. The total study duration is 2 (run-in phase) + 8 (study phase) = 10 weeks per patient. An overview of the study is shown in Fig. 1.

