#### Secondary endpoints

Secondary endpoints include: 1) intradialytic LV chamber quantification and deformation (longitudinal function with speckle tracking) and LV diastolic function; 2) the intradialytic hemodynamic profile of SBP, DBP, MAP and PP; 3) organ and tissue damage, such as the release of specific cellular components; and 4) patient-reported symptoms and thermal perceptions during each modality.

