#### Data management

Clinical data will be extracted from the hospital’s electronic information systems and dialysis machines. Data will be collected on electronic case record forms (CRF) using web-based Castor EDC [61]. Data will be entered in the data file by an experienced research nurse or research physician. Beforehand, ranges will be defined in the electronic file for all data values to ensure their validity and integrity. Data entry will be checked for 5% of randomly selected CRFs. Patient data will be coded. Analyzing and publication of the results of this study will be performed anonymously.

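### The off-line echo reading is not exempted from the open design, so the reader may know modality and time point; masked reading of coded clips would be a cheap improvement

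*Protocol article*

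**What the plan says.** The *Study design* section gives one masking status for the whole trial: "The HOLLANT study is an open, cross-over, multicenter, intervention RCT". It makes no separate statement about outcome assessors.

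The *2D speckle tracking echocardiography* section fixes when the images are taken: "Speckle Tracking Echocardiography (STE) will be performed before, after 1 and after 3 h of treatment during the last dialysis of each modality". It names the scanner, transducer and software version, and lists biplane volumes and ejection fraction, global and regional strain, and diastolic and right ventricular measures. On the reading it says: "The data will be recorded electronically and assessed off-line by a trained research physician". It does not say whether that physician can see the modality, the period or the hour.

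The *Secondary endpoints* section lists these measures as its first item: "1) intradialytic LV chamber quantification and deformation (longitudinal function with speckle tracking) and LV diastolic function". The numbering is not declared to be a hierarchy.

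The *Data management* section says "Data will be entered in the data file by an experienced research nurse or research physician" and "Patient data will be coded". The second statement is the only mention of coding in the article.

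**The concern.** Biplane volumes, ejection fraction and strain depend on which frame is chosen and how the border is traced, so the reader's judgement enters the value. The trial also has a declared direction: *Objectives* and *Discussion* are framed around an advantage for HV-HDF. A reader who shares that expectation and knows the modality could, without intent, measure HV-HDF clips more favourably.

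The *Discussion* names the cross-over as the study's largest strength because differences between patients cannot influence the results. That protection does not extend to an expectation that changes with modality within the same patient. The *Discussion* also plans to correlate echo changes with intradialytic hemodynamics and with biochemical signs of myocardial damage. A distorted reading could therefore reach the mechanistic conclusions as well as the comparison of modalities.

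**Working it through.** The article gives no figure for this endpoint (no standard deviation, effect size, reader variability or power for strain), so there is no figure to reproduce. The check is a comparison of sections plus one line of algebra.

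**Inputs**
- Masking status: open, no exception stated (*Study design*).
- Reading: off-line, by a research physician, masking not mentioned (*2D speckle tracking echocardiography*).
- Coding: patient data only (*Data management*). Coding a patient's identity does not hide which modality or hour a clip belongs to.
- Studies per completing patient: 3 time points × 4 modalities = 12.
- Primary endpoint: systolic pressure from a cuff connected to the dialysis machine (*Primary endpoint*, *Hemodynamic monitoring*).

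**Step 1: what the text permits.** Taken together, these sections allow a reader who knows the modality and hour of all 12 studies. Such a reader would break no stated rule.

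**Step 2: what the cross-over cancels.** Write the value read for patient i, modality j and hour t as

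y(i,j,t) = p(i) + m(j,t) + b(j,t) + error,

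where p is the patient's own level, m the true modality effect and b the shift due to the reader's expectation. The difference between modalities j and k in one patient is

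y(i,j,t) − y(i,k,t) = [m(j,t) − m(k,t)] + [b(j,t) − b(k,t)] + error.

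The patient term p(i) drops out. The reader term does not, and it cannot be told apart from the true effect. The random intercepts and slopes planned in *Statistical methods* do not change this, because b is tied to modality in the same way as m.

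**Step 3: why the hour matters.** If the analysis uses change from the pre-dialysis reading, a shift that is equal at all hours of a session cancels. A shift applied only to the 1 h and 3 h clips does not, and that requires the reader to know the hour as well as the modality. Hiding modality removes the source of a modality-linked shift; hiding the hour adds protection if the modality is guessed.

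**Step 4: correlations.** If blood pressure truly differs between modalities, a b(j,t) that follows the same ordering creates an association between strain and pressure even where none exists.

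**Step 5: reach.** The primary endpoint is not measured by the echo reader, so b does not enter it.

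**The case against.** The strongest objection is that this builds on silence. The article condenses a fuller protocol that is not shown, and masked reading or clip coding could be described there or in an imaging manual. The word open describes how treatment is given and does not by itself settle how stored images are read. This much stands: a reader might infer that the images are definitely read unmasked, and the documents do not support that. What remains is that the article states a masking status, describes the echo procedure in detail and makes no exception for the reading, where such an exception would normally be stated.

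Other stronger readings also fail:

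- *The echo reader also enters the treatment data.* *Data management* names a research nurse or research physician but does not say that this is the person who reads the echoes.
- *The inflation of false-positive findings can be quantified.* With 32 completers (40 less 20%, from *Sample size considerations*) and a two-sided 5% paired test, P(|Z + d√32| > 1.96) is about 0.20, 0.40 and 0.81 for shifts d of 0.2, 0.3 and 0.5 standard deviations of the within-patient difference. The arithmetic is right, but the shifts are assumed and nothing in the article supports any of them. The planned analysis is a mixed model, not a paired test. The section on COVID-19 also warns that cardiac ultrasounds may be undesirable, so fewer than 32 patients may have complete echo data. These figures do not estimate the bias.
- *Masking would remove the bias at no cost.* It would reduce reading bias only. Views are acquired at the bedside during an open treatment, and the hour may be partly visible in the images.
- *The main result is at risk.* It is not; only secondary echo outcomes are concerned.

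**Conclusion.** The point holds as a cheap improvement. The trial is open, the off-line reading is not exempted, and the measures depend on judgement. As written, the reader may know modality and time point, and any expectation tied to modality would go uncancelled into the comparison of readings and the planned correlations.

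The size of the bias is unknown and cannot be derived from the article; it may be zero. The conclusion assumes that the shown text is the operative description of the reading and that frame choice and tracing leave room for judgement. If the full protocol already provides masked reading, only a sentence in the article is lacking.

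**What to change.** Add to the *2D speckle tracking echocardiography* section that:

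- existing staff code the stored clips, with modality, period and, as far as possible, hour removed;
- a physician without access to the key reads them in random order;
- the key is joined only after the readings are locked;
- the same procedure covers clips of patients already enrolled.

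If masked reading is already in place, state it.

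The cost is file coding and possibly some re-reading, with no extra visit and no burden for patients. *Trial status* reports 25 of 40 patients included, so at most 25 × 12 = 300 stored studies would need recoding, and 40 × 12 = 480 over the whole trial if every patient completed every echo. Re-reading is needed only for clips already measured with modality visible. The change does not address acquisition at the bedside, and the report should say so.

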#### Blood sampling

Blood sampling will be performed in the last session of each dialysis modality, after the long interdialytic interval (see Fig. 1). Blood samples will be drawn from the arterial line of the extracorporeal circuit (ECC) before treatment (but after administration of LMWH) and after 4 h of treatment (see Table 2). After processing, all blood samples will be stored at − 80 °C until assessment in the central laboratory of the hospital of the Amsterdam University Medical Centers.

#### Markers of inflammation, cardiac- and endothelial damage and FGF23

Soluble CD14 (sCD14), interleukin-6 receptor (IL-6R), high sensitive C-reactive protein (hs-CRP), creatine kinase myocardial band (CK-MB), soluble vascular intercellular cell adhesion molecule 1 (sv-ICAM-1), and fibroblast growth factor 23 C-terminal (FGF23 C-term) will be assessed in EDTA or heparin plasma samples after being placed on ice and centrifuged within 30 min, at 1800 g for 10 min.

#### Relative blood volume and oxygenation

Hematocrit measurements, reflecting relative blood volume (RBV), and spO2 will be assessed continuously in the ECC by the HCT sensor and with the integrated spO2-monitoring device located on the Dialog iQ® dialysis machine (B. Braun Avitum AG, Melsungen Germany). RBV- and spO2 values will be read out from the trend-files, which are retrieved by service technicians. In addition, blood samples for pO2, pH, bicarbonate and base excess analysis will be drawn from the arterial line before and after treatment (at the moment of activation and before de-activation of the oxygen saturation monitoring device on the Dialog iQ®), and assessed directly with a point-of-care device (Epoc blood analysis, Epocal Inc., Ottawa, ON, Canada).

#### Bacterial DNA

Microbial DNA (mDNA) will be assessed in EDTA blood with 16S–23S interspace (IS) pro after DNA isolation. In short, IS-pro is a eubacterial PCR-based technique for detection of most bacterial species within a sample, and is based on length and sequence polymorphisms of the bacterial 16S–23S ribosomal interspace regions. IS-pro has been optimized to detect bacterial loads as low as 1 CFU per 5 ml blood [57, 58].

#### Extracellular vesicles

Citrate blood samples will be centrifuged for 15 min at 2500 g, 20 °C to remove red blood cells. Subsequently, the EV-containing supernatant is isolated and centrifuged again (15 min at 2500 g, 20 °C). The EV-containing supernatant will be frozen and stored at − 80 °C until further use. Before assessment, samples will be thawed at 37 °C. Subsequently, direct measurement of the EVs in plasma will take place, as extensively described by van der Pol et al. [59].

### Endpoints

#### Primary endpoint

The primary endpoint of this study is an absolute intradialytic nadir in SBP of < 90 and < 100 mmHg for patients with a predialysis SBP < 159 and ≥ 160, respectively.

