**Methods:**

HOLLANT is a Dutch multicentre randomized controlled cross-over trial. In total, 40 prevalent dialysis patients will be included and, after a run-in phase, exposed to standard HD, HD with cooled dialysate, low-volume HDF and high-volume HDF (Dialog iQ® machine) in a randomized fashion. The primary endpoint is an intradialytic nadir in systolic blood pressure (SBP) of < 90 and < 100 mmHg for patients with predialysis SBP < 159 and ≥ 160 mmHg, respectively. The main secondary outcomes are 1) intradialytic left ventricle (LV) chamber quantification and deformation, 2) intradialytic hemodynamic profile of SBP, diastolic blood pressure (DBP), mean arterial pressure (MAP) and pulse pressure (PP), 3) organ and tissue damage, such as the release of specific cellular components, and 4) patient reported symptoms and thermal perceptions during each modality.

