Since IDH is a frequently occurring side-effect of HD treatment and microcirculatory dysfunction is a prominent feature of patients with advanced chronic kidney disease (CKD) [17, 18], every single dialysis session may further deteriorate the already affected structure and function of vital organs, such as the brain, gut and heart [19]. After all, HD-associated cardiomyopathy may result not only from the various inflammatory and metabolic derangements of pre-dialysis CKD [20], but also from HD-induced perfusion deficits [21–27], which is considered a model of repetitive organ ischemia-reperfusion injury. In this respect it is interesting to note that an absolute intradialytic nadir of SBP < 90 and < 100 mmHg for patients with a predialysis SBP < 159 and ≥ 160 mmHg, respectively, appeared most strongly associated with mortality in a large study, comparing the relation between various definitions of IDH and outcome [28]. Considering the gut, HD-induced hypoperfusion may cause disruption of the intestinal barrier and permit the translocation of gut-derived endotoxins, bacterial DNA and/or intact bacteria into the blood. Circulating bacterial fragments may contribute to systemic inflammation, cardiovascular disease, and reduced survival in these patients [29–34].

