**Inclusion criteria**	
- Patients treated with HD or HDF 3 x per week during at least 4 h for at least 2 months.	
- Ability to understand study procedures.	
- Willingness to provide informed consent.	
- Dialysis single-pool Kt/V for urea (spKt/Vurea) ≥ 1.2^a^	
- Achievement of a blood flow of ≥350 ml/min and/or convection volume of ≥23 Liter per treatment during the run-in phase.	
- Dialysis access recirculation < 10%^a^.	

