### Statistical methods

Descriptive data will be represented as mean ± standard deviation (SD), median (interquartile range) or number (percentage), when appropriate. The between-treatment number of IDH episodes (based on an intradialytic nadir in SBP as described above) will be analyzed using regression analysis with a Poisson distribution. The mean inter-treatment variability of continuous variables will be calculated using generalized linear mixed effects models with a random intercept, random slope or both, based on the lowest Aikaike’s Information Criterion. A two-sided *p-*value ≤0.05 is considered statistically significant. Statistical evaluations will be performed using IBM SPSS Statistics version 26.0 (Chicago, IL, USA) or RStudio version 1.1.456.

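### The primary endpoint's predialysis SBP strata are not contiguous: a reading of 159 mmHg has no nadir limit, which leaves IDH status open for nadirs of 90–99 mmHg (minor)

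*Protocol article*

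**What the plan says.** The Primary endpoint section makes the outcome a lowest SBP during the session of under 90 or under 100 mmHg, the limit depending on the stratum: "patients with a predialysis SBP < 159 and ≥ 160, respectively". The abstract's Methods paragraph gives the same strata, "for patients with predialysis SBP < 159 and ≥ 160 mmHg, respectively". So does the Background, where the definition is taken from a cited study of several IDH definitions: "for patients with a predialysis SBP < 159 and ≥ 160 mmHg, respectively".

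The definition feeds the primary analysis directly, as Statistical methods shows: "The between-treatment number of IDH episodes (based on an intradialytic nadir in SBP as described above) will be analyzed using regression analysis with a Poisson". Under Hemodynamic monitoring, blood pressure "will be recorded before, after and during each dialysis treatment every 30 min" in the first week of each modality, and every 15 minutes in the second. Every session should therefore yield a predialysis SBP and a nadir. The article does not state the resolution of the cuff readings, and it gives no rule for a predialysis value of 159.

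**The concern.** A two-stratum rule should assign every possible value to one stratum. Here the lower stratum stops short of 159 and the upper one starts at 160. The affected rule is the classification threshold of the primary endpoint, and the two nadir limits differ by 10 mmHg, so the stratum chosen can decide whether a session is an event.

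If the gap is still open when the data are analysed, someone has to choose a limit for those sessions, and the study is open-label. Alternatively, code that follows the text literally could set such sessions to missing, or let them default to non-events. The second outcome would discard even a nadir below 90 mmHg, which is an event under either limit.

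**Working it through.** The plan states no figure to reproduce here. The check is an enumeration, followed by a rough sizing.

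**1. Which values are unassigned?** Each whole-number predialysis SBP from 60 to 260 mmHg was tested against the two conditions (below 159; 160 or above). Exactly one value, 159, meets neither. If decimals are recorded, the gap is 159.0–159.9.

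**2. At 159 mmHg, when does the choice of limit matter?**

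| Nadir SBP (mmHg) | Event under the below-90 limit | Event under the below-100 limit | Limits agree |
|---|---|---|---|
| below 90 | yes | yes | yes |
| 90–99 | no | yes | **no** |
| 100 or above | no | no | yes |

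Only a nadir of 90–99 is undetermined, that is, a fall of 159 − 99 = 60 to 159 − 90 = 69 mmHg.

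**3. How many sessions read 159?**

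Inputs from the article:
- 40 patients, with about 20% loss expected (Sample size considerations), so 40 × 0.80 = 32 completers.
- Three sessions a week, from the inclusion criteria: "Patients treated with HD or HDF 3 x per week during at least 4 h for at least 2 months".
- Eight study weeks, from Study design: "The total study duration is 2 (run-in phase) + 8 (study phase) = 10 weeks per patient". This gives 8 × 3 = 24 sessions per patient.
- The Discussion calls the first week of every modality a wash-out. If only second weeks count, there are 4 × 3 = 12 sessions per patient.

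Assumptions not in the article: predialysis SBP is normal with mean μ = 135–150 and SD σ = 20–25 mmHg, readings are rounded to whole mmHg, and the stratum is set from each session's own predialysis reading.

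Formula: P(159) = Φ((159.5 − μ)/σ) − Φ((158.5 − μ)/σ).

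| μ | σ | P(159) |
|---|---|---|
| 135 | 20 | 0.0097 |
| 135 | 25 | 0.0101 |
| 150 | 25 | 0.0150 |
| 150 | 20 | 0.0180 |

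Multiplying the lowest and highest values by the number of sessions:

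| Sessions | 40 patients | 32 completers |
|---|---|---|
| Both weeks | 960: 9.3 to 17.3 | 768: 7.5 to 13.8 |
| Second week only | 480: 4.7 to 8.6 | 384: 3.7 to 6.9 |

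Wider assumptions (mean 130–150, SD 18–25) give 0.6–2.0%, or about 6–19 of 960.

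**4. How many are ambiguous in substance?** The counts in step 3 must be multiplied by the probability of a nadir of 90–99 given a predialysis value of 159, for which the article gives no figure. If it is assumed to be 5–20%, the range is 9.3 × 0.05 = 0.5 to 17.3 × 0.20 = 3.5 of 960 sessions, or 4.7 × 0.05 = 0.2 to 8.6 × 0.20 = 1.7 of 480, spread over four modalities.

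**The case against.** The strongest reply is that this is an obvious slip of the inequality sign. Next to a stratum that starts at 160, most readers would take the lower one to include 159. A convention for a single integer is also something that an analysis plan commonly settles, and none is shown here. Much of this stands. It makes a serious consequence unlikely, and the article gives no ground for predicting that the gap will be programmed as printed. It does not remove the error, because the definition is given in full three times with the same gap. Nor can the slip be confirmed from the article: the definition comes from a cited source that is not available here, so which boundary was intended remains unproven.

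Three stronger readings are tempting, and the article supports none of them.

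- A reader might infer that no session at 159 mmHg can be classified. The two limits disagree only for nadirs of 90–99.
- A reader might take 9–17 sessions as the number lost or misclassified. That range counts all sessions reading 159, under an assumed distribution. The wash-out week may halve it, since the article does not say outright which weeks enter the primary analysis.
- A reader might infer a bias, or an influence magnified by a small number of events. Any single rule would apply alike to all four modalities within the same patients, and the article gives no expected IDH count or rate.

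Whether the limit is set per session or once per patient is a separate question and is not argued here.

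**Conclusion.** The point holds, as a minor one. As written, the primary endpoint assigns no nadir limit to a predialysis SBP of 159 mmHg, and no other part of the article supplies one. That conclusion follows from the wording alone and needs no assumption. Its size does rest on assumptions: with the normal distribution above, about 1.0–1.8% of sessions fall in the gap, and only those with a nadir of 90–99 mmHg are truly undetermined, plausibly from none to a few sessions in the whole trial. Design, power and interpretation are unaffected. It is still worth correcting, because it concerns the rule that creates the primary outcome and the correction is nearly free.

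**What to change.** Reconcile the abstract, the Background and the Primary endpoint section with the intended definition so that the two strata meet. One wording that does so is below 160 and 160 or above. It leaves the stated upper stratum unchanged and works whether or not decimals are recorded; 159 or below is equivalent only for whole-mmHg readings. The sponsor should check this against the source of the definition, since the article does not show which boundary was meant.

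The same rule should be written into the specification for the primary analysis before the data are analysed. When the article was written, 25 of the intended 40 patients had been included, so there was still time. The cost is one character in three places and one line of the specification. No change to data collection is needed, because predialysis SBP and the intradialytic readings are already recorded.
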